### Patient questionnaires

Patients will complete questionnaires at each visit for up to six weeks (Table 1 provides domains covered, and the Additional File (Appendices 4 and 5) includes the questionnaires). Patients will also complete online questionnaires at 3 months, 6 months and 12 months post-index visit (see Additional file 1: Appendix 6). Figure 1 documents the patient data collection time points throughout the study.

**Fig. 1 Fig1:**
[figure not shown]
Flow chart of participant recruitment and data collection

### Administrative data

Participating patients will be followed for 12 months using Ontario health administrative data held by the Ontario Institute for Clinical Evaluative Sciences (ICES) to determine if any imaging was undertaken (plain x-ray, CT scan, MRI, fluoroscopy, positron emission tomography (PET) scan, ultrasound). Although plain x-ray, CT scan and/or MRI are most likely to be ordered for patients with low back pain, we will capture all related imaging to be comprehensive in the assessment of inappropriate imaging. ICES data will also capture whether a pathological condition develops (defined with diagnoses at more than two healthcare visits), and surgery and emergency visits related to such a condition.

Some imaging may not be captured by the administrative data. Approximately 12% of chiropractors take their own plain x-rays and this information will not be captured in ICES data [58]; completed encounter forms by these chiropractors will indicate whether they took lumbar x-rays, and this information will also be collected via the patient-completed questionnaires. Also, some patients in Ontario elect to go to a private facility outside Ontario and individually pay for imaging. This information will be captured via the patient-completed questionnaires.

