### Encounter data

After each patient consultation during the data collection period, participating clinicians will complete a handwritten 1-page encounter form (see Additional file 1: Appendix 3) for each of 25 consecutive consenting eligible patients with low back pain. There is one type of form for the initial encounter, and another, briefer form, for any follow-up consultations for the same low back pain episode. The encounter form is a modified form previously used in a chiropractic setting to systematically collect clinical data [51]; chiropractors reported that completing the form took 2–3 min per patient. The encounter forms for this project were piloted by two chiropractors, three physiotherapists and two family practitioners, who each recruited between two to five patients with low back pain over a six week period. Only minor changes were made to the form after the pilot study.

At the time of the patient’s initial consultation clinicians will record: key history and clinical findings; working diagnosis; diagnostic imaging ordered/taken; interventions provided or recommended; who is paying for the consultation; and, OHIP number for linkage purposes. Follow up encounter forms will be completed for each visit for up to 6 weeks to determine if any clinical indications for imaging arise. Six weeks was chosen because this is the time when people with low back pain are likely to be recovered, if pain is persisting they have progressed to the sub-acute stage, or if they have a pathological cause this is likely to be definitively diagnosed [57].

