### Quantitative data analyses

Characteristics of clinicians, patients and encounters will be summarised using descriptive statistics. We will calculate imaging rates per 100 low back pain patients with 95% confidence intervals and we will determine imaging rates for each primary care profession. We will undertake multilevel logistic regression analysis to determine the effects of clinician- and patient-level factors on inappropriate imaging. Clinician-level factors assessed will include age, sex, profession type, location of clinician training, clinician years in practice, ownership of imaging facilities, knowledge of imaging guidelines, and time spent with patient. Patient-level factors measured at baseline will include age, sex, race/ethnicity, insurance status, living in a metropolitan area, beliefs about usefulness of imaging, education level, duration/severity of low back pain, and three month measurement of satisfaction with treatment and adverse events. Patients consulting each clinician will form a cluster and will be considered as the second level in the multilevel logistic regression. We will also conduct a marginal logistic regression analysis to investigate the effects of clinician- and patient-level factors on inappropriate imaging and estimate the association between inappropriate imaging and explanatory factors in the marginal model using Generalised Estimating Equations. The analysis will allow examination of differences in results from the two models and determine whether the conclusions depend unduly on the model assumptions.

### Methods for study 2

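### After week six, in-house chiropractic x-rays are recorded only by patient self-report while other Ontario imaging stays in ICES, so outcome capture differs by imaging ownership and by profession

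*Protocol article*

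**What the plan says.** The Administrative data section of the protocol article sets a 12-month follow-up for imaging through ICES. It then names an exception: "Approximately 12% of chiropractors take their own plain x-rays and this information will not be captured in ICES data". The stated remedy is that "completed encounter forms by these chiropractors will indicate whether they took lumbar x-rays, and this information will also be collected via the patient-completed questionnaires".

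Two other sections set how long those substitutes run. Under Encounter data: "Follow up encounter forms will be completed for each visit for up to 6 weeks to determine if any clinical indications for imaging arise". Under Patient questionnaires: "Patients will complete questionnaires at each visit for up to six weeks", and then "Patients will also complete online questionnaires at 3 months, 6 months and 12 months post-index visit".

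The Inappropriate imaging section combines encounter, questionnaire and administrative data to classify the outcome. Under Quantitative data analyses, profession type is a clinician-level factor in the multilevel logistic model, and so are "ownership of imaging facilities, knowledge of imaging guidelines". Imaging rates are also to be reported for each profession.

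**The concern.** The remedy for in-house x-rays is described as two sources, but one of them, the encounter form, covers only six weeks of a 12-month window. After that the clinic has no record that reaches the study, and ICES has none either. Only the patient's online answer remains. For other imaging done in Ontario, ICES continues to record without any action by patient or clinician.

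How completely the outcome is seen therefore depends on two of the factors being tested. A patient who has a late in-house x-ray and does not answer, or does not report it, has no imaging on record and will look like a patient who was not imaged. If that happens at all often, the ownership association is pulled toward no effect, and a weak estimate could not be told apart from poor capture. The study is meant to guide knowledge translation strategies, so whether owning imaging equipment goes with more inappropriate imaging is a result that readers will use.

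**Working it through.** The plan states no figure on this point, so there is nothing to reproduce. The check has two parts: which source covers which period, and how much an assumed loss would matter.

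**1. Sources for an in-house chiropractic x-ray**

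| Source | Index visit to week 6 | Week 6 to month 12 |
|---|---|---|
| ICES | no | no |
| Encounter form | yes | no |
| Visit questionnaire | yes | no |
| Online questionnaire | not before month 3 | months 3, 6 and 12 |

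Other Ontario imaging is in ICES in both columns. The gap lies in the second column and affects clinics that take their own x-rays.

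**2. Number affected.** With 50 chiropractors planned and about 12% taking their own x-rays, 0.12 × 50 = 6 clinicians. At up to 25 patients each, 6 × 25 = 150 patients.

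**3. Inputs for the size of the bias.** None of these except the 12% is given for this purpose in the article, so they are assumptions.
- Rate in non-owner clinics: 10%, the lower end of the base-rate range in Sample size justification (10 to 45%).
- True rate in owner clinics: 20%, 30% or 45%.
- L, the share of imaged owner-clinic patients whose only imaging is an in-house x-ray after week six: 0.10 to 0.50.
- M, the share of those that the online questionnaires miss: 0.20 to 0.60.
- Chiropractors who own imaging facilities are taken to be the same as those who take their own x-rays, with equal patients per chiropractor.

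**4. Ownership odds ratio.** Observed owner rate = true rate × (1 − L × M). The product L × M runs from 0.10 × 0.20 = 0.02 to 0.50 × 0.60 = 0.30.

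| True owner rate | True odds ratio against 10% | Observed rate | Observed odds ratio |
|---|---|---|---|
| 20% | 2.25 | 19.6% to 14.0% | 2.19 to 1.47 |
| 30% | 3.86 | 29.4% to 21.0% | 3.75 to 2.39 |
| 45% | 7.36 | 44.1% to 31.5% | 7.10 to 4.14 |

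Example: 20% × (1 − 0.30) = 14%, and (0.14/0.86)/(0.10/0.90) = 1.47. With M = 0 there is no bias.

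**5. Chiropractic rate.** Loss = 0.12 × owner rate × L × M. Smallest: 0.12 × 20% × 0.02 = 0.05 percentage points. Largest: 0.12 × 45% × 0.30 = 1.6 points.

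**6. Against sampling error.** With the article's intracluster correlation of 0.088 and cluster size of 25, the design effect is 1 + 24 × 0.088 = 3.11, so 150 patients carry the information of about 150/3.11 = 48. At a 20% rate the 95% margin is about 1.96 × √(0.20 × 0.80/48) = 11 points, against a shift of 0.4 to 6.0 points from step 4.

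**The case against.** The article discloses the gap and does name a source for the later period. Bias therefore needs non-response or under-reporting. No rate is given for either, and the online questionnaire itself (Appendix 6) is not shown. This stands, and it is why the bias can be called likely but not certain.

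Only plain x-rays are taken in-house. CT, MRI and x-rays done elsewhere in Ontario still reach ICES, and a patient already recorded as imaged in the first six weeks loses nothing. This also stands, and it limits L.

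The 12% refers to chiropractors who take their own x-rays, while the ownership item in Table 2 goes to all clinicians. The article does not say that the two groups coincide, so their overlap is an assumption. Private imaging outside Ontario also rests on self-report, but it is not tied to clinician ownership and cannot be presumed to offset the gap.

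The secondary objective on professions concerns recommending imaging, and the initial encounter form records what was ordered or taken. That softens the profession side. Even so, the article also plans to report imaging rates by profession and bases its power statement on comparing inappropriate imaging rates among professions.

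The ownership estimate rests on few clinics, and the shift at a 20% owner rate lies within sampling error. True, but imprecision is visible in a confidence interval and a one-directional loss is not.

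Finally, sensitivity analyses are often left to a fuller document. Their absence is not the point here. The point is that the data windows, as fixed in the article, make capture depend on tested factors.

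**Conclusion.** The point holds as a difference in capture after week six, with likely downward bias of unknown size. It may be material for the ownership effect: from 2.25 to 2.19 at the mild end and from 7.36 to 4.14 at the strong end. It is small for the chiropractic rate, at most about 1.6 points under the same assumptions, against the 6-point difference used in the power statement. The direction assumes that missed late x-rays are not offset by false-positive self-reports.

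A reader might infer two stronger things. One is that the estimates are certainly biased. The documents do not show this, because complete self-report would remove the bias. The other is that the ownership association could turn around. A calculation on late imaging alone can show that: 15% against 10% is an odds ratio of 1.59, and if half of the owners' x-rays are missed, 7.5% against 10% is 0.73. But it leaves out the x-rays recorded in the first six weeks, takes all of the owners' late imaging to be in-house, and assumes a 50% loss that nothing in the article supports. Over the whole outcome, no combination in the table falls below 1.47. Even at L × M = 0.30, reversal would need a true owner rate below 10%/0.70 = 14.3%, that is, a true odds ratio under 1.5.

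**What to change.** - Keep the 12-month outcome as it is.
- Add a pre-specified analysis of the ownership effect and the profession comparison restricted to imaging from the index visit to six weeks, where encounter forms cover in-house x-rays and ICES covers other Ontario imaging. Confirm that the briefer follow-up form carries the x-ray item, and say whether an image is dated by order or by performance, since referred imaging may be done later than an in-house x-ray.
- For the profession comparison only, add a 12-month sensitivity analysis that leaves out patients of chiropractors who take their own x-rays. It cannot serve the ownership effect, because it removes the exposed group.
- State that the 12-month ownership estimate depends on questionnaire response and is likely conservative.

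No new data are needed. The cost is analysis wording and two further analyses. The six-week analysis has fewer events and answers a narrower question, which is why it should stand beside the 12-month result and not replace it. Private imaging outside Ontario would still rest on self-report in either window.

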### Inappropriate imaging

The encounter, questionnaire and administrative data will be used to determine if any imaging ordered is inappropriate. We will apply a modified version of the American College of Radiology imaging appropriateness criteria for low back pain [59]. If any of the following situations occur, including signs or symptoms indicating suspicion of “red flag” conditions [60], imaging will be considered appropriate: infection, tumour, fracture, or cauda equina syndrome (Table 3). If the clinical, questionnaire and administrative data are not suggestive of any of these conditions, any lumbar imaging ordered will be deemed inappropriate.

**Table 3 Tab3:** Diagnostic imaging will be deemed inappropriate in the absence of these conditions that indicate a specific cause of low back pain [59]

Condition	Sign or symptom
Cancer	History of cancer; unexplained weight loss
Infection	Immunosuppression; intravenous drug use
Fracture	Prolonged use of corticosteroids; history of significant trauma; minor fall or heavy lift in a potentially osteoporotic or elderly individual
Cauda equina syndrome	Acute onset of urinary retention or overflow incontinence; faecal incontinence; saddle anaesthesia

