#### Data collection and data sources

Table 1 and Table 2 describes the patient-level and clinician-level factors that we hypothesise may be associated with inappropriate imaging.

**Table 1 Tab1:** Patient-level factors being measured that may be associated with inappropriate imaging

Factor	Questionnaire items	Timing				
		*First visit*	*Follow up visits*	*3-month Q*	*6-month Q*	*12-month Q*
Age	Single questionnaire item	X				
Sex	Single questionnaire item	X				
Education level	Single questionnaire item	X				
Socio-economic status	Two questionnaire items: Postal code and education level	X				
Race/ethnicity	Single questionnaire item	X				
Living arrangement	Single questionnaire item	X				
Insurance status	Single questionnaire item	X				
Compensation status (workplace injury or motor vehicle)	Single questionnaire item	X				
Patient expectations of imaging	Single questionnaire item	X	X			
Patient beliefs about imaging	Two questionnaire items [43]	X				
Duration of low back pain	Single questionnaire item	X				
Previous history of low back pain	Single questionnaire item	X				
Low back pain intensity	Single questionnaire item (pain right now)	X	X	X	X	X
Leg pain intensity	Single questionnaire item (pain right now)	X	X	X	X	X
Recovery expectations	Single questionnaire item	X	X			
Previous back surgery	Single questionnaire item	X				
Previous medication and non-medication treatment	Single questionnaire items	X				
Previous imaging	Single questionnaire item	X				
General Health	Single questionnaire item	X	X			
Physical activity level	Single questionnaire item	X				
Overweight or obesity	Two questionnaire items: Self-reported height and weight	X				
Possible pathological cause of back pain (fracture, infection, cancer, cauda equina syndrome)	Questionnaire items about: Trauma; History of cancer; Unexplained weight loss; IV drug user; Long term use of oral steroids	X	X	X	X	X
Anxiety	Two questionnaire items [73]	X	X			
Depression	Two questionnaire items [73]	X	X			
Confidence in ability to work and to live a normal lifestyle	Two questionnaire items	X	X			
Disability	Questionnaire items: Roland Morris Q [74]	X		X	X	X
STarT Back risk category	Questionnaire items: STarT Back questionnaire [75, 76]	X		X	X	X
Fear avoidance	Single questionnaire item 14 from the Tampa Scale for Kinesiophobia (TSK) [77]^a^	X	X			
Pain Catastrophizing	Single questionnaire item 3 from Pain Catastrophizing Scale (PCS) [78]^a^	X	X			

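### The rule for inappropriate imaging pools data up to 12 months and does not require the indication to precede the image

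*Protocol article*

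**What the plan says.** The first primary objective in the protocol article is the rate of inappropriate lumbar imaging and the factors associated with it. The section Inappropriate imaging defines the outcome.

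- **Sources:** "The encounter, questionnaire and administrative data will be used to determine if any imaging ordered is inappropriate".
- **When imaging is appropriate:** if any of the listed situations occurs, including signs or symptoms that raise suspicion, "imaging will be considered appropriate: infection, tumour, fracture, or cauda equina syndrome (Table 3").
- **When it is inappropriate:** "If the clinical, questionnaire and administrative data are not suggestive of any of these conditions, any lumbar imaging ordered will be deemed inappropriate".

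Three other places set the time span of these sources.

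- **Administrative data:** "Participating patients will be followed for 12 months using Ontario health administrative data". The same section adds: "ICES data will also capture whether a pathological condition develops (defined with diagnoses at more than two healthcare visits").
- **Table 1, row on possible pathological cause:** "Questionnaire items about: Trauma; History of cancer; Unexplained weight loss; IV drug user; Long term use of oral steroids". This row is marked for the first visit, follow-up visits and the 3-, 6- and 12-month questionnaires.
- **Encounter data:** "Follow up encounter forms will be completed for each visit for up to 6 weeks to determine if any clinical indications for imaging arise".

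**The concern.** Whether an image was indicated depends on what was known, or could have been known, when it was ordered. The stated rule pools three sources and sets no time order between indication and image. It also counts the conditions themselves, not only prior suspicion of them. As worded, the test is run on the patient's pooled data and the result is applied to any lumbar image that patient had.

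Two kinds of image could then be classed wrongly:

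- A first-visit x-ray with no indication becomes appropriate if the patient reports new trauma at a later questionnaire.
- An unindicated image that happens to show a fracture or tumour becomes appropriate because of its own finding. That mixes diagnostic yield with indication.

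The rate and the factor analysis both use this outcome. Patients with more visits or more completed questionnaires have more chances to be reclassified, so the comparison of professions and the odds ratios could be affected as well as the overall rate.

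**Working it through.** The outcome definition has no figure of its own to reproduce. The check is first on the text, then an illustration of size.

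**1. Does any sentence impose a time order?**

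| Place | Window | Must the indication precede the image? |
|---|---|---|
| Inappropriate imaging (the rule) | none stated | no |
| Table 1, red-flag items | first visit to 12 months | no |
| Administrative data | 12 months | no |
| Encounter data | up to 6 weeks, encounter forms only | no |

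The encounter-form window is the only short one, and it does not limit the other two sources.

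**2. Can the pooled data postdate the image?** Yes. The administrative definition of pathology needs diagnoses at more than two visits, so at least three. For an image ordered at the first visit, a condition that develops during follow-up can meet that count only after the order.

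**3. Direction.** Under the literal rule, later information can add a reason to call an image appropriate but can never remove one. Against an at-order standard, the inappropriate rate can therefore only fall.

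**4. Size (illustration).** Let p be the inappropriate rate at ordering and f the share of those images reclassified by later data. Then:

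observed rate = p × (1 − f)

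The values 10% and 45% for p are the ends of the range of base imaging rates in Sample size justification. The document gives no value for f; those below are assumptions.

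| p | f = 2% | f = 5% | f = 10% | f = 20% |
|---|---|---|---|---|
| 10% | 9.8% | 9.5% | 9.0% | 8.0% |
| 45% | 44.1% | 42.75% | 40.5% | 36.0% |

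**5. The one internal anchor.** Background says that up to 99% of primary care patients have non-specific pain. If about 1% have a specific cause, diagnoses alone could move at most about 1 percentage point of patients, and only if all of them had been imaged without a prior indication. Later reports of trauma, weight loss or steroid use come on top, and the document gives no rate for them.

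**6. Uneven reclassification.** Take the 6-point difference between professions that the sample size section targets, placed at 39% v 45%.

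- f = 5% in both: 45 × 0.95 − 39 × 0.95 = 42.75 − 37.05 = 5.7 points.
- f = 2% in the lower group, 10% in the higher: 45 × 0.90 − 39 × 0.98 = 40.5 − 38.22 = 2.3 points.
- f = 10% in the lower group, 2% in the higher: 45 × 0.98 − 39 × 0.90 = 44.1 − 35.1 = 9.0 points.

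An equal f barely changes the contrast. An unequal f could shrink or inflate it, but nothing in the document shows that f differs by profession.

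**The case against.** The strongest reply is that no any-time rule is written. The section names sources and criteria, and matching each image to its indication by date could be left to a full protocol or analysis plan. The text also leans towards judgement by indication: it speaks of suspicion, most Table 3 entries are prior history, and the follow-up encounter forms are meant to catch indications as they arise. Imaging is itself tracked for 12 months, so a late image needs red-flag information from about the same time. The repeated items in Table 1 are therefore no proof of backward reclassification.

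Much of this stands. A reader might infer that the protocol says outright that later events override the status at ordering. It does not; that follows only from the pooling and the absence of a time clause. But these points show a legitimate use for repeated data without supplying the missing clause. The rule is stated as operative, and followed literally it can give the wrong class, so this is more than omitted detail.

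A second reply is that some use of later data corrects error. A cancer history or long-term steroid use first recorded at a later visit may well have existed at ordering. This stands: a strict rule based on recording dates would misclassify such patients in the other direction, and the fix has to allow for it.

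A related argument is that patients later shown to have a specific cause fall outside the non-specific population in the objective. If that is the intent, they should leave the denominator as well. The rule as written changes only the class of the image.

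A third reply is that the size is unsupported. This also stands. Every value of f above is assumed.

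**Conclusion.** The concern holds for the rule as worded. It pools questionnaire and administrative data to 12 months, counts the conditions themselves, and does not require the indication to precede the image. Relative to an at-order standard, the error runs one way, towards a lower inappropriate-imaging rate. It may be uneven across patients or professions.

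The size cannot be computed from the document. The part due to diagnoses is probably near 1% of patients, if the Background figure applies. The part due to later red-flag reports is unknown.

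Two stronger readings are not supported. One is that the rate is understated by a known or large amount, or that the profession contrast is in fact distorted; both depend on assumed reclassification shares. The other is that all use of later data is wrong. Later data are proper for later images and for pre-existing history that was recorded late.

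**What to change.** Add a time clause to the primary outcome definition:

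- Classify each image separately, on signs, symptoms, history and diagnoses present on or before its order date. Use the imaging service date where no order date is held.
- Count pre-existing history, such as prior cancer or long-term steroid use, even if it was first recorded later.
- Do not count the image's own findings or events that arise after the order.
- Report pathology found later as a separate outcome.
- Show the any-time rule as a sensitivity analysis. The gap between the two rates then measures the size that cannot be computed now.

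The cost is wording and some programming on data already planned, with no new follow-up. The drawback is that some onset and order dates must be approximated by visit, claim or questionnaire dates. Fee-code claims and self-reported private imaging may carry no order date, and a questionnaire's completion date is not an onset date. The approximation rules should be fixed before analysis.
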